### Randomisation and blinding

An independent statistician created a randomisation schedule, which was then given to the lead trial pharmacist at each site. Participants are blindly randomised in a 1:1 ratio between groups, using the variable 8-block randomisation schedule of 80 codes per site to maintain blinding. Stratification occurs at each of the four sites (aiming for a 1:1 random allocation at each site). Randomisation and group allocation happen after enrolment (informed consent) and prior to Day 1 of the study, enabling study medications to be prepared by the study pharmacist at each site. The randomisation schedule and nabiximols and placebo canisters are only identifiable to trial pharmacists at each site, who themselves have no contact with participants. All participants, clinicians and researchers involved in service delivery, data collection and analysis remain blinded to group allocation (active or placebo) until the end of the study.

### Clinical intervention

#### Study medications

Nabiximols is an oromucosal spray delivered through a mechanically actuated pump, with each spray delivering 100 μL (2.7 mg THC and 2.5 mg CBD). The placebo medication consists of an alcohol base and peppermint oil flavouring present in the active nabiximols medication, but does not include any cannabinoids and plant-based terpenoids. A previous study [13] demonstrated the ability to maintain blind dosing of nabiximols versus placebo in cannabis dependent patients in an inpatient setting. All dispensed medication canisters are labelled with the subjects’ name, trial site, week number, medication dose, expiry date and prescribing doctors’ name.

The proposed dosing regimen for nabiximols is based upon experience from previous studies with cannabis dependent patients [13, 29, 30], and the principles of dose titration used in similar clinical paradigms (opioid agonist replacement therapy). Nabiximols and placebo doses are individually titrated by the SMO with each participant to optimise clinical effect (reduce cravings and withdrawal) and safety (avoidance of side effects, such as intoxication). Doses are reviewed and titrated by the clinician and the patient regularly (daily for first two days of Week 1, then at weekly intervals). Day 1 dose is two sprays (5.4 mg THC, 5.0 mg CBD) four times a day (QID), days 2 and 3 maximum dose is four sprays (10.8 mg THC, 10 mg CBD) QID. Thereafter, the maximum daily doses during the ‘maintenance’ period (to end week 12) are 32 sprays (86.4 mg THC, 80 mg CBD) per day divided into four doses (21.6 mg THC, 20 mg CBD QID). These nabiximols doses are considerably greater than those conventionally used for treating other indications (e.g. a daily maximum dose for multiple sclerosis is 32.4 mg THC, 30 mg CBD), reflecting the high THC tolerance of cannabis dependent individuals and the need for high doses to effectively ameliorate withdrawal symptoms and cravings. During week 13, participants have the option of tapered reductions of their study medication at approximately 10-15% per day, in order to minimise any medication discontinuation effects (e.g. withdrawal).

#### Clinical reviews

Weekly clinical reviews with a nurse and/or SMO include: a Time Line Follow Back (TLFB) [34] of their use of study medication, cannabis, nicotine, alcohol and other drugs in the past week since last clinical review; a review of any adverse events; separate participant and clinician assessment of medication dose adequacy (using a 5-point Likert scale e.g. 1 = ‘much too low’, 3 = ‘about right’ to 5 = ‘much too high’); participant rating of cannabis withdrawal severity using Cannabis Withdrawal Scale (CWS) [35], general physical and mental health and psychosocial conditions, examination (including blood pressure (BP), pulse rate (PR), evidence of intoxication or withdrawal, or other findings of note) and the opportunity to address other issues identified by the participant. In addition to weekly reviews conducted by nursing staff (baseline, days 1 and 2, weeks 3, 5, 6, 7, 9, 10, and 11), the SMO reviews the participant at weeks 2, 4, 8 and 12, at which time they also formally assess any adverse events reported since the last medical review and complete the Australian Treatment Outcomes Profile (ATOP) [36], a validated clinician-completed instrument that includes participant ratings of physical and mental health and range of clinical risks, such as, child protection, violence, homelessness) and the Brief Psychiatric Rating Scale (BPRS) [37] to formally assesses psychiatric symptoms that may occur with high dose THC use [38]. The SMO assess whether the participant is globally deteriorating and warrants study discontinuation. See Table 1 for schedule of events.

#### Psychosocial intervention

In conjunction with receiving medication treatment, participants are provided with a minimum of six structured counselling sessions based on cognitive behavioural therapy (CBT) [39]. The CBT sessions use a range of strategies and interventions, such as, understanding cannabis and the patient, preparing the patient for change and various strategies, ways to manage withdrawal and relapse prevention. Participation in the counselling program is encouraged, and all participants must attend at least 2 sessions (an initial assessment and one further follow up) in order to continue in the study. Participants may negotiate additional counselling sessions with the therapist beyond the 12-week intervention period. Counsellors complete de-identified research Clinical Record Forms (CRFs) after each session to identify themes or areas covered according to the CBT intervention as a strategy to record adherence with the counselling intervention.

### Outcome and treatment process measures

Outcome measures for each of the study objectives are described below, and summarised in Tables 1 and 2.

**Table 2 Tab2:** Table of all clinical and research measures included in study

Domain	Name	Description of measure	How and when administered
Basic	Demographics	10 Questions: basic demographics including; age, gender, employment, relationship status, education level, living situation and Aboriginal and Torres Strait Islander background.	Research Interview: Week 0 (baseline) day 1
Cannabis Use	Cannabis Use	4 semi-structured questions: exploring frequency, amount and method of cannabis use in the last 4-weeks	Research Interview: Weeks 0, 4, 8, 12, 24
	Cannabis Withdrawal Scale (CWS) [35]	19 items on a 10-point Likert Scale, with 0 = Not at all to 10 = Extremely. The CWS is used as a diagnostic instrument in clinical and research settings to assess cannabis withdrawal symptoms. Participants are asked how they feel over the last 24 h in 8 domains; irritability, depression, anxiety, cannabis cravings, physical symptoms, sleep difficulty, restlessness and appetite.	Research Interview and Clinical Reviews: Weekly
	Marijuana Craving Questionnaire-short form (MCQ) [66]	12 items on a 7-point Likert scale, with 1 = strongly disagree to 7 = strongly agree. The MCQ is a self-report instrument that assesses marijuana craving along 4 dimensions; compulsivity, emotionality, expectancy and purposefulness.	Research Interview: Weeks 0, 4, 8, 12, 24
	Cannabis Problems Questionnaire (Adult revised- CPQ-R) [67]	27 items on a 11-point Likert scale, with 0 = doesn’t apply to me to 10 = strongly apply to me. The CPQ-R measures acute and physical consequences, psychological consequences, and social consequences of cannabis use.	Research Interview: Weeks 0, 4, 8, 12, 24
	Self-coping and efficacy for quitting cannabis questionnaire [68]	20 items on a 7-point Likert scale, with 1 = not at all confident to 7 = very confident. Participants are asked to indicated their confidence in their ability to resist the temptation to use cannabis in a variety of interpersonal and intrapersonal situations.	Research Interview: Weeks 0, 4, 8, 12, 24
	Modified Time Line Follow Back *(adapted)* [40]	Using a modified Time Line Follow Back approach examining cannabis use in preceding 4 week period.	Research Interview: Weeks 0, 4, 8, 12, 24
Other Substance Use	Australian Treatment Outcome Profile (ATOP) [36]	3 Part Questionnaire:	Research Interview: Weeks 0, 4, 8, 12, 24
		1. Substance use; items refer to substance use over the last 4-weeks, in particular: alcohol, amphetamines, benzodiazepines, heroin, other opioids, cocaine, other substances and tobacco.	
		2. Injecting risk behaviour; 2-items exploring injecting behaviour in the last 4-weeks.	
		3.Health and Well-being; 11-items investigating the participants’ accommodation arrangements, psychological and physical health and quality of life.	
	FagerstrÖm Test for nicotine dependence (FTND) [69]	6 item questionnaire that measures nicotine dependency, with a total available score of 10.	Research Interview: Weeks 0, 4, 8, 12, 24
	The Alcohol Use Disorders Identification Test (AUDIT) [70]	10 item questionnaire covering domains of alcohol consumption, drinking behaviour and alcohol related problems. Responses to each question are scored from 0 to 4, giving a maximum possible score of 40.	Research Interview: Weeks 0, 4, 8, 12, 24
	Opioid Related Behaviours in Treatment (ORBIT) scale *(modified)* [71]	8 item questionnaire on a 5-point Likert scale ranging from 0 = never to 4 = very often. The questionnaire explores opioid-related behaviours that are divergent, unexpected, non-adherence to medication, unsanctioned diversion of medication to others, hazardous use or misuse. ORBIT questions modified for cannabis dependent population.	Research Interview: Week 12
Mental Health	Depression, Anxiety and Stress scale (DASS) Short-form [51]	21 item questionnaire on a 4-point Likert scale, ranging from 0 = did not apply to me at all to 3 = applied to me very much or most pf the time. The DASS 21 measures the severity of symptoms of depression, anxiety and stress and enables clinicians to measure a patient’s response to treatment.	Research Interview: Weeks 0, 4, 8, 12, 24
	Primary Care Post Traumatic Stress Disorder (PC-PTSD) [72]	4 item questionnaire that explores whether a patient has ever experienced a traumatic event (e.g. a serious accident, physical/sexual assault/abuse, natural or political disaster etc.) over the course of their life. If so, participants answer a series of Yes/No questions.	Research Interview: Weeks 0, 4, 8, 12, 24
	Brief Psychiatric Rating Scale (BPRS) [37]	18 item questionnaire on a 7-point Likert scale, ranging from 1 = not present to 7 = extremely severe. Clinicians measure psychiatric symptoms such as depression, anxiety, hallucinations and unusual behaviour.	Research Interview: Weeks 0, 4, 8, 12, 24
Physical Health	Short form 36 health survey questionnaire (SF-36) [50]	36 item questionnaire using a mixed scale. Domains covered in the survey include; physical functioning, role limitations due to physical problems, social functioning, bodily pain, general mental health, role limitations due to emotional problems, vitality and general health problems.	Research Interview: Weeks 0, 4, 8, 12, 24
	Brief Pain Inventory - Short form (BPI) [53]	5 items taken from Brief Pain Inventory-Short form using a 10-point Likert scale, ranging from 0-no pain to 10 = worst pain imaginable. Participants are asked to think about any abnormal pain experienced in the last 7 days and rate the intensity and interference of the pain in the participants’ life.	Research Interview: Weeks 0, 4, 8, 12, 24
	Athens Insomnia Scale (AIS) [54]	7 item questionnaire using a 4-point Likert scale ranging from 0 = none to 4 = very severe. The AIS is a self-assessment psychometric instrument designed for quantifying sleep difficulty based on the ICD-10 criteria.	Research Interview: Weeks 0, 4, 8, 12, 24
	Sheehan Disability Scale (SDS) [73]	3 item instrument using a 10-point Likert scale ranging from 0 = not at all to 10 = very severe. The SDS asks participants to best rate their impairment with work, social life/leisure activities and family life/home responsibilities.	Research Interview: Weeks 0, 4, 8, 12, 24
	Visual Analogue Scale of client ratings on medication effects [42]	5 item questionnaire using a scale from 0 to 100 measuring subjective liking and strength of drug effect, comparability to cannabis, sedation, bad effects and subjective physiological effects	Research Interview: Weeks 0, 4, 8, 12, 24
Social/ Other	Opioid Treatment Index- Crime (OTI-Crime) [55]	8 questions modified from the full Opioid Treatment Index. The modified version concentrates on questions relating to criminality and focuses on the frequency of recent criminal behaviour in four areas: property crime, drug dealing, fraud and crimes involving violence.	Research Interview: Weeks 0, 4, 8, 12, 24
	Health and Work Performance Questionnaire (HPQ) -Short Form Absenteeism and Presenteeism [74]	4 Questions modified from the Health and Work Performance questionnaire (HPQ). The HPQ is designed to estimate the workplace costs of health problems in terms of reduced job performance, sickness absence, and work-related accidents/injuries.	Research Interview: Weeks 0, 4, 8, 12, 24
	National Evaluation of Pharmacotherapies for Opioid Dependence (NEPOD) - Health Service Utilisation (HSU) [75]	5 questions adapted from the NEPOD study. The HSU section of the NEPOD focusses on health services used in the last 4-weeks, frequency of use and cost of service to the participant.	Research Interview: Weeks 0, 4, 8, 12, 24
	Testing the Blind	5 questions exploring the participants’ subjective opinion of study drug allocation.	Research Interview: Weeks 4, 8, 12, 24
	Patient’s Global Impression of Change Scale (PGICS) [64]	1 question modified from the Global Rating of Change (GLOC) survey exploring the participants’ subjective opinion of change since starting study.	Day: 85
Cognitive Assessment	Wechsler Test of Adult Reading (WTAR) [61]	Verbal pronunciation of 50 words with irregular phoneme-to-grampheme conversion. Total correct recorded	Research Interview: Weeks 0
	Eriksen Arrow Flankers (with no-go) [56]	Speed of response to target stimuli flanked with either neutral, congruent or incongruent stimuli (24 each). Random 10% (*n* = 8) trials require with-holding of response (no-go). Reaction time; errors and false alarms recorded	Research Interview: Weeks 0, 4, 24
	1,2,3-Back Task [58]	Identification of repetition in a rapid sequence of stimuli, either 1, 2, or 3 stimuli prior (30, 75, 75 stimuli respectively; 25% targets). Reaction time, accuracy, false-positives recorded	Research Interview: Weeks 0, 4, 24
	Symbol-Digit Substitution Task (SDMT) [59]	Decoding symbols related to presented digit; 87 trials; Reaction Time and Accuracy recorded	Research Interview: Weeks 0, 4, 24
	Stop-Signal Task (SST) [57]	Withholding of already initiated motor response after a delay; 12 target trials of 48; reaction time, errors, stop signal response time recorded	Research Interview: Weeks 0, 4, 24
	Rapid Visual Information Processing (RVIP) [60]	Response to high working memory load (3 back) stimuli; 24 targets in 300 stimuli; reaction time; accuracy and false positive responses recorded	Research Interview: Weeks 0, 4, 24
	Rey Auditory Verbal Learning Task [62]	Retention of a 15 item word list presented on 5 occasions. Number of words recalled on each presentation, following presentation of a novel list of 15 words; and then after brief and long delays recorded. Recognition of target stimuli also assessed.	Research Interview: Weeks 0, 4, 24

#### Objective 1

To examine cannabis treatment efficacy outcomes, including changes in illicit cannabis use during treatment and treatment retention.Illicit cannabis use is quantified as self-reported number of days of illicit cannabis use and average daily amount of cannabis use in grams at the 4 weekly research interviews using modified Timeline Followback [40] techniques. The primary end-point is self-reported illicit cannabis use days during the maintenance phase of treatment (weeks 1-12). Objective measures of illicit cannabis use will be determined from weekly urine collection with quantitative analysis of urinary THC, THC-COOH, CBD and other cannabinoids. 4-weekly point prevalence abstinence during maintenance phase (weeks 1-4, 5-8, 9-12), and post-treatment period (week 24) will be ascertained by combining self-report data from researcher interviews and urinalysis.Treatment retention (days in protocol treatment) are recorded from clinical records. Participants who do not attend for more than two consecutive weeks are deemed to have dropped out of treatment, and the last scheduled day of dosing is calculated as the end of treatment date.

#### Objective 2

To examine the adverse event profile, and the abuse liability of nabiximols as a take home treatment for cannabis use disorder.Adverse events are assessed and addressed during clinical assessments with the study medical officer at 4-weekly appointments. At the end of study participation, the SMO records the severity of each AE (mild, moderate, severe), the outcome (ongoing or resolved, with or without treatment), and attribution to study medication.Abuse liability: Adherence to study medication is estimated by participants returning their medication canisters at the weekly clinical review and weighing the amounts of medication used (equivalent to a pill count). Aberrant medication behaviours (missed doses, extra ‘unsanctioned’ doses, misuse or diversion) are assessed by self-report at researcher interviews using the modified ORBIT [41], a validated aberrant medication behaviours self-report instrument. In addition, a series of subjective assessments of abuse liability using the Visual Analogue Scale (VAS) [42], (0-100) of subjective liking, comparability to cannabis, strength of effect and subjective physiological effects are conducted 4-weekly at researcher interviews.

#### Objective 3

To assess the costs and health related quality of life (HRQoL) associated with the provision of nabiximols for treatment of resistant cannabis use disorder and the potential societal savings (decreased health care, improved productivity, and changes in criminal behaviors).Cost effectiveness: Consistent with other drug treatment cost effectiveness evaluations [43–45], the primary outcome is Quality Adjusted Life Years (QALY) measured by the SF-6D [46], (at 4 weekly research interviews) determined using area under the curve analysis [47] for each individual. Resources included are all clinical services provided as trial interventions (see Treatment Process Measures below), adverse event management, self-reported health care utilization outside of the trial (hospital, emergency department, primary care and other specialist health services) as well as self-reported participation in criminal activity that will be costed using unit costs (CPI adjusted if necessary) [48]. Lost productivity and personal costs are collected by structured self-report (WHO Health and Performance Questionnaire: Clinical Trials Version) [49]. The costs will be summed and combined with the outcome measure, and the incremental cost-effectiveness ratio [ICER = (C_Nabiximols_-C_Control_)/(E_Nabiximols_-E_Control_)] calculated.

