## Methods

### Study design

This project is a phase III multisite (four-sites) outpatient randomised double-blind placebo controlled parallel design comparing a 12-week course of buccally administered nabiximols to placebo (Fig. 1). Both groups receive structured ‘best practice’ individual counselling based on cognitive behavioural therapy principles, regular case management and clinical reviews over the course of the trial. Medications (nabiximols, placebo) are dispensed on a weekly basis, and study medication is discontinued in week 12 using tapering doses. Participants are followed up at week 24, 12 weeks after discontinuation of nabiximols/placebo treatment. All participants are also followed-up for confidential research interviews, (irrespective of completion of the trial intervention) at baseline (week 0), weeks 4, 8, 12 and 24. Overview of study procedures and sequence of events is provided in Table 1.

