### Research procedures

#### Research interviews

The research assistant at each site conducts research interviews at weeks 0 (baseline), 4, 8, 12 and week 24. Details of the instruments and timing of administration are shown in Table 2.

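### Outside-trial health-service use in weeks 13-20 is not collected, so an ICER taken to week 24 would have an 8-week hole in its costs; the plan should fix one horizon for costs and QALYs

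*Protocol article*

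**What the plan says.** The places that bear on this are all in the protocol article.

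- **Service-use recall (Table 2, Social/Other, NEPOD Health Service Utilisation).** "The HSU section of the NEPOD focusses on health services used in the last 4-weeks, frequency of use and cost of service to the participant". The row lists weeks 0, 4, 8, 12 and 24.
- **Interview schedule (Research interviews).** "The research assistant at each site conducts research interviews at weeks 0 (baseline), 4, 8, 12 and week 24". Study design adds: "Participants are followed up at week 24, 12 weeks after discontinuation of nabiximols/placebo treatment".
- **QALY (Objective 3).** The text says "the primary outcome is Quality Adjusted Life Years (QALY) measured by the SF-6D [46], (at 4 weekly research interviews", and that the QALY is "determined using area under the curve analysis [47] for each individual". Table 1 places the SF-6D at weeks 0, 4, 8, 12 and 24.
- **Costs (Objective 3).** The resources are trial interventions, management of adverse events, self-reported health care outside the trial, crime, lost productivity and personal costs. Then: "The costs will be summed and combined with the outcome measure, and the incremental cost-effectiveness ratio" is calculated.
- **Source of trial-service data (Treatment process measures).** Participation in trial interventions is recorded on clinical record forms, not by 4-week recall.

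No end week is given for the QALY, the costs or the ICER.

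**The concern.** An ICER needs its numerator and denominator to cover the same period. The visit schedule has a 12-week interval between weeks 12 and 24. An area under the curve bridges that interval by joining two utility values. A 4-week recall question does not: the week-24 interview looks back only to week 20.

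The unasked weeks start just after study medication ends, when any difference between arms in relapse and related service use might appear. The Background reports that after an earlier 6-day nabiximols course, relapse was frequent in both groups but came later with nabiximols. That does not show that costs will differ here, but it is a reason not to assume that they will not.

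Data that were never asked for cannot be recovered by a later analysis plan. They can only be imputed.

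**Working it through.** The article prints no figure for the economic analysis, so there is none to reproduce.

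**1. Weeks covered by recall.** Inputs: 4-week look-back (Table 2); post-baseline interviews at weeks 4, 8, 12 and 24.

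| Interview | Weeks covered |
|---|---|
| 4 | 1-4 |
| 8 | 5-8 |
| 12 | 9-12 |
| 24 | 21-24 |

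The week-0 interview covers time before treatment. Total covered: 4 × 4 = 16 of 24 weeks. Uncovered: weeks 13-20, that is 8/24 = 33% of follow-up and 8/12 = 67% of the time after week 12. Weeks 1-12 are fully covered (12 of 12).

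**2. Weeks covered by the QALY.** Trapezoidal weights, in weeks, for utilities at 0, 4, 8, 12 and 24 are 2, 4, 4, 8 and 6, which sum to 24. The segment from week 12 to 24 is 12/24, half of the area. Stopped at week 12, the weights are 2, 4, 4 and 2, which sum to 12.

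**3. Which horizon is meant?** Objective 3 calls the interviews 4-weekly, which taken literally fits weeks 0-12. But the article uses the same expression for measures that also run to week 24. The text gives the SF-36 and the visual analogue ratings as 4-weekly, and Table 2 lists both at weeks 0, 4, 8, 12 and 24. Table 1 does the same for the SF-6D itself. The wording leans towards the full schedule but does not settle it.

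**4. Effect on a 24-week ICER.** Let d be the mean weekly cost difference (nabiximols minus placebo) from outside-trial services in weeks 13-20, and ΔQ the QALY difference. If costs are summed without those weeks, the ICER changes by −8d/ΔQ.

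Illustration on assumed values only: utility gain 0.02 from week 4 on, and a cost difference of 50 currency units per week in weeks 1-12.

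- ΔQ to week 24 = 0.02 × (4 + 4 + 8 + 6)/52 = 0.00846.
- ΔQ to week 12 = 0.02 × (4 + 4 + 2)/52 = 0.00385.

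| Weekly cost difference after week 12 | 24-week ICER, all weeks | 24-week ICER, weeks 13-20 missing |
|---|---|---|
| +50 | (600 + 600)/0.00846 = 141,818 | (600 + 200)/0.00846 = 94,545 |
| 0 | 600/0.00846 = 70,909 | 70,909 |
| −50 | (600 − 600)/0.00846 = 0 | (600 − 200)/0.00846 = 47,273 |

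(ICERs use unrounded ΔQ.) The 12-week ICER is 600/0.00385 = 156,000 in every row, with no gap. So the missing weeks can lower the ICER, raise it or leave it unchanged.

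**5. Baseline utility (separate, precision only).** With 71 per arm, the standard error of the baseline SF-6D difference is SD × √(2/71). For an assumed SD of 0.10 to 0.15 this is 0.0168 to 0.0252. If a difference of one standard error persisted in full for 24 weeks, it would contribute 0.0168 × 24/52 = 0.0077 to 0.0252 × 24/52 = 0.0116 QALY. Full persistence is an extreme case.

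**The case against.** The strongest reply is that no contradiction is written down. The article states no ICER horizon. The primary efficacy endpoint is set in weeks 1-12, interviews are literally 4-weekly only up to week 12, and at that horizon recall and QALYs match exactly. Horizon and handling of unobserved intervals can also sit in a health-economic plan that is not shown. This stands as far as it goes: a reader might infer that the ICER mixes two horizons, and the document does not establish that. It does not remove the collection gap, which an analysis plan can only impute.

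Other inferences go further than the text:

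- **That nothing in weeks 13-20 is costed.** Trial services, including the week-13 dispensing and nursing review in Table 1, come from record forms.
- **That the gap extends to crime and productivity.** The crime items ask about recent behaviour without a stated window, and the work-performance row gives no recall period.
- **That missing weeks are counted as zero.** Plain summing would do that, but the article does not say so, and a fuller plan might interpolate.
- **That an unadjusted QALY difference is biased.** Under randomisation it is unbiased. Adjustment is a matter of precision, and the general ICER formula does not exclude it.

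It is also fair that a longer recall is less exact and would make week 24 less comparable with earlier visits.

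**Conclusion.** The point holds in conditional form. As described, the schedule leaves outside-trial health-service use uncollected in 8 of 24 weeks, which are 8 of the 12 weeks after week 12. An ICER taken to week 24 would lack these costs while its QALYs span the whole period. The bias is −8d/ΔQ if the weeks are simply left out; its sign and size cannot be known beforehand, and it is nil if d is zero. A 12-week ICER does not have this problem.

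This rests on two assumptions: that the adapted questionnaire keeps its 4-week window at week 24, as Table 2 says, and that no other source of outside-trial service use exists, since the article names none. The currency figures are illustrative and estimate nothing in this trial.

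The point deserves attention because cost-effectiveness is a declared primary objective and the loss is permanent once week-24 interviews are done. The baseline-utility suggestion is a minor addition on which the main point does not depend.

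**What to change.** State one horizon for costs and QALYs.

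- **If 24 weeks and week-24 interviews are still to come:** have the form ask about service use since the week-12 interview, keeping the last 4 weeks as a separate block so that week 24 stays comparable with earlier visits. The cost is one extra recall block on one form; the downside is less exact recall over the longer period.
- **If 24 weeks and interviews are done:** interpolate weeks 13-20 from the observed 4-week blocks, state the rule in advance, and report a 12-week ICER as a sensitivity analysis.
- **Otherwise:** restrict both costs and QALYs to weeks 0-12, and say how week-13 trial services are treated. This costs a sentence or two, but the ICER then says nothing about the period after treatment.

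State the recall periods for crime and productivity as well, so that they can be checked against the same horizon.

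Separately, estimate the QALY difference by regression on arm, baseline SF-6D and site, in place of the plain difference in individual areas. Baseline SF-6D is already collected and site is the stratification factor, so this needs no new data.
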